## Abstract

*Background*. Recent reports suggest that a proportion of tinnitus patients suffer from mental illness. Autonomic nervous system plays a useful role in tinnitus therapy since electrical vagal nerve stimulation (VNS) has been frequently used to alleviate tinnitus-induced depression in clinic. heart rate variability (HRV), which is reflective of autonomic nervous system function, has been proved to be modulated by acupuncture. In the present study, we aim to compare the effect of deqi sensation on heart rate variability in adult tinnitus patients. *Methods*. Thirty participants are randomly assigned to verum acupuncture (creating deqi) or shallow acupuncture (not creating deqi) at Baihui (Du-20), Shenting (Du-24), Tinghui (GB-2), Waiguan (SJ-5), and Zulinqi (GB-41) for 3 weeks. The primary outcome measure is heart rate variability, which is measured at the first acupuncture, as well as the last acupuncture. *Discussion*. Completion of this trial will help to identify the role of deqi sensation in acupuncture effect for tinnitus and reveal an autonomic modulation mechanism for acupuncture effect. *Trial Registration*. This trial is registered with International Standard Randomised Controlled Trial Number ISRCTN58013563.

## 1. Background

Tinnitus is generally defined as a perception of sound in the absence of an external acoustic stimulus. Subjective tinnitus affects approximately more than 600 million individuals worldwide [1, 2]. It has a prevalence of roughly 12–15% in the adult population [3–5]. The amount of distress in people suffering from tinnitus can be evaluated by validated tinnitus questionnaires. The imbalance of autonomic system leads to further increases in the sensitivity of the auditory system and reinforcement of the attentional filters, which makes tinnitus loudness and awareness more severe. This, in turn, exacerbates the level of stress and so on, making the tinnitus progressively worse over time [6]. A number of clinical trials have demonstrated the presence of psychopathological disorders and high depressive scores in tinnitus patients [7, 8]. For this reason, there may be a causal relationship between the molecular bases of these disorders. As a the neurotransmitter of the parasympathetic nervous system, acetylcholine (ACh) is likely to play a role in plasticity at many sites in the auditory system [9]. Animal models of tinnitus demonstrate changes in cholinergic mechanisms in auditory nuclei [10]. The cholinergic signaling is involved in many physiological functions and in some disease states such as anxiety and depression [11]. It is suggested that the limbic and autonomous nervous systems are largely responsible for troublesome tinnitus [12]. These findings in the literature suggest an association among ANS, depression, and tinnitus. Heart rate variability (HRV), as a simple and noninvasive quantitative marker of autonomic function [13, 14], has the potential to evaluate the autonomic status of tinnitus patients. 

Acupuncture, as a particularly complementary and alternative medicine (CAM), has frequently been used to treat tinnitus [15, 16]. It can improve the symptoms of tinnitus by the activating of endogenous opioid mechanisms and neuropeptides which stimulate specific brain structures [17]. Acupuncture can relieve the loudness and disturbing quality tinnitus immediately, and significantly improve the quality of life, tension and sleep [18]. During the verum acupuncture, needles create the specific needle sensation called “deqi” (“aching,” “dull,” “heavy,” “numb,” “radiating,” “spreading” and “tingling”) at specific acupuncture points [19]. Deqi is suggested to be the main mechanisms producing effects from acupuncture [20], by generating a release of spinal and supraspinal beta-endorphins, proinflammatory neuropeptides and an increase in peripheral circulation [21]. However, there is lack of adequate experimental data to indicate the relationship between deqi sensation and modulation effect of acupuncture on ANS [22]. Therefore, more evidences are needed to prove the specific effect of acupuncture. The aim of our study is to evaluate the effect of deqi on HRV in tinnitus patients. 

## 2. Methods

We perform the study according to common guidelines for clinical trials (Declaration of Helsinki, International Conference on Harmonisation (ICH)/WHO Good Clinical Practice standards (GCP) including certification by an external audit). It will strictly follow the CONSORT statement to report high-quality study results. The trial protocol has been approved by the Research Ethical Committee of Beijing Hospital of Traditional Chinese Medicine affiliated to Capital Medical University (Ref: 201213). This trial was registered with ISRCTN at Current Controlled Trials (ISRCTN58013563). 

### 2.1. Recruitment

Patients will be recruited in acupuncture clinic, Beijing Hospital of Traditional Chinese Medicine affiliated to Capital Medical University with a target sample size of 30 subjects. The trial is executed from March 2012 to June 2013.

### 2.2. Inclusion Criteria

Patients who meet all of the following conditions will be considered for enrollment [23]: typical conditions of unilateral or bilateral tinnitus,aged 18–65, either sex,tinnitus duration of more than 3 months, not receiving any treatment last 1 month,normal language and intelligence ability to answer and fill in the questionnaire,better understanding of acupuncture, and good compliance to the research observation and evaluation,written and informed consent. 

### 2.3. Exclusion Criteria

Objectivity tinnitus (objective tinnitus is audible to the examining/auscultating physician),acute or intermittent tinnitus, history of Meniere disease, or tinnitus induced by middle ear/inner ear/small pons angle tumor, underlying disease or history: otitis media, tympanic membrane perforation, or eustachian tube function obstacle,acoustic neuroma, intracranial damage or use of any ototoxic drugs,severe dysfunction of heart, kidneys or liver, the serious original disease of hematopoietic system or endocrine system, serious aphasia, depression syndrome or mental disease.

### 2.4. Randomisation and Blinding

After participants complete a baseline evaluation, a research coordinator ([name]) who is uninvolved with data collection randomly allocates them to either verum acupuncture group or shallow acupuncture group by using a computer-generated, blocked random-allocation sequence with a block size of 6. The random codes are only known by another researcher ([name]) who is not involved in treatment and statistical analysis.

The assignment is done in a single-blind manner, in which the patients are blinded to treatment assignment. In order to minimize the placebo effects, patients are informed in a manner suggesting that two different types of acupuncture treatment are compared. One type is traditional acupuncture, another is novel acupuncture, and the effect of both is uncertain. Similar strategies of informed consent have been used in most previous acupuncture trials [24]. HRV analysis and assessment of THI are performed by a researcher ([name]), who is blinded to patients' treatment respectively. During the intervention, acupuncturist and all the researcher personnel are segregated immediately after the treatment starts and are instructed not to exchange information with each other.

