### 2.5. Interventions

This trial is a randomized controlled study. Participants will receive acupuncture for 3 weeks (Figure 1) (twice per week). All candidates go through a standardized interview and receive more information about the study and the treatments. They also undergo audiological testing of hearing thresholds, minimal masking levels, and loudness discomfort levels carried out by an audiologist in Tongren Hospital affiliated to Capital Medical University ([name]).

Timepoints are as follow: visit 1: screening, visit 2: treatment initiation, participants will receive acupuncture for 3 weeks, visit 3: 3 weeks later of first acupuncture, followup and treatment finish.

Patients who meet the inclusion criteria and none of the exclusion criteria are randomized to one of two treatment groups. Group A will receive verum acupuncture (creating deqi sensation). Group B will receive shallow acupuncture (not creating deqi sensation).

Acupuncture points are selected as follow (Figure 2).

Patients are stimulated by 5 main acupoints: Baihui (Du-20), Shenting (Du-24), Tinghui (GB-2), Waiguan (SJ-5), and Zulinqi (GB-41). The acupoints are stimulated continuously by the true needles or the shallows for 20 minutes per session. 

Acupuncture is performed with sterile needles by one therapist ([name]) with more than 22 years of experience and an acupuncture license from the Chinese medicine practitioner from the Ministry of Health of China. Treatment will be conducted over a period of 3 weeks, at a frequency of 2 sessions/week. No additional treatment is allowed.

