## 3. Discussion

This trial has been designed above to identify whether acupuncture could (verum acupuncture or shallow acupuncture) treat subjective tinnitus patients by modulating HRV, so as to explain the mechanism of acupuncture effects on tinnitus. If this questionnaire results provide evidence for the safety of acupuncture, more patients with these conditions may be encouraged to seek out acupuncture. 

The present study aimed to help to draw more attention in acupuncture's potential for treating patients with tinnitus by autonomic regulation. Although a climate where acupuncture might be assumed to be ineffective exists [27, 28], there is inadequate evidence on which to base a judgment on acupuncture's effectiveness for tinnitus. Well-designed randomized controlled trials which can provide the acupuncture effect mechanism for tinnitus by scientific approach are needed.

Verum acupuncture is administered by twirling and lifting the needles until deqi occurred. One of the greatest challenges in acupuncture research is selecting an appropriate sham acupuncture control. There are several existing sham acupuncture methods including shallow needling on acupoint, shallow needling on nonacupoint and ritualized mock acupuncture. To avoide the difference of acupoint selection, shallow needling on acupoint is used as a control group in this trials. For the shallow group, the point selection is the same as the verum acupuncture group. However, the depth of needles inserted vertically to the subcutaneous level should be rigidly controlled over no more than 3 mm. Any sensation (deqi) or needle manipulation is prohibited in this group. Because the needles are inserted at the same points, the patients cannot distinguish the shallow acupuncture from the real one on the vision. 

Placebo effects of acupuncture are actively studied in many articles, and sham acupuncture is a representative method for an acupuncture placebo tool [29, 30]. But there is a lack of consensus on the most valid approach to establishing placebo acupuncture. Therefore, important aspects of the placebo acupuncture control need to be considered. In this trial, we will evaluate the effect of deqi on HRV and reveal the potential mechanism of acupuncture treatment for tinnitus.

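### A single fixed block size of 6, with one necessarily unblinded therapist in a one-clinic trial, is an avoidable predictability risk: on average 7.5 of 30 allocations could be deduced by someone who knows the block size and all earlier allocations

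*Protocol article*

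**What the plan says.** Section 2.4 (Randomisation and Blinding) specifies a "computer-generated, blocked random-allocation sequence with a block size of 6". No other block size is given, so the size is taken as constant.

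The setting is described elsewhere in the article:

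- **One recruiting clinic** (Section 2.1): "Patients will be recruited in acupuncture clinic" of a single hospital, "with a target sample size of 30 subjects".
- **One therapist** (Section 2.5): "Acupuncture is performed with sterile needles by one therapist".
- **Blinding** (Section 2.4): "The assignment is done in a single-blind manner, in which the patients are blinded to treatment assignment". The researcher who analyses heart rate variability (HRV) and assesses the Tinnitus Handicap Inventory (THI) is also blinded.
- **The therapist cannot be blind** (Discussion): "Verum acupuncture is administered by twirling and lifting the needles until deqi occurred", while manipulation and deqi are prohibited in the shallow arm.
- **Eligibility** (Section 2.2) includes the patient's understanding of acupuncture and good compliance, with no threshold for either.

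Section 2.4 also sets four safeguards. A coordinator outside data collection makes the allocation. Allocation follows the baseline evaluation. The codes are known only to another researcher, who takes no part in treatment or statistical analysis. The acupuncturist and the research staff are kept apart once treatment starts and told not to exchange information.

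**The concern.** With a constant block size, the end of each block follows from what came before it: once one arm has used its places, the rest of the block is determined. Concealing the list does not prevent this, because the inference needs only the block size and the earlier allocations. The therapist delivers every treatment and so learns every allocation. The coordinator who allocates is in a similar position.

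Foreknowledge does harm only if it reaches a decision about who enters, or when. The criteria on understanding of acupuncture and on compliance leave room for judgement, and a patient can be deferred or declined before randomisation. If that happened with the next arm known, the arms could differ systematically from the start. With about 15 patients per arm, a few such decisions could matter. Adjustment could deal with imbalance on measured baseline factors but not with unmeasured selection.

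**Working it through.** The article gives no predictability figure, so there is none to reproduce.

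**Inputs**

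- Block size 6 (Section 2.4).
- Two arms (Section 2.5): "Patients who meet the inclusion criteria and none of the exclusion criteria are randomized to one of two treatment groups". The ratio is not stated; 1:1, that is 3 + 3 per block, is assumed.
- 30 patients (Section 2.1), which is 30 / 6 = 5 complete blocks.
- No stratification is mentioned; a single sequence is assumed.
- The observer knows the block size and all earlier allocations in randomisation order. The therapist does so if patients start treatment in that order.

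**Certain allocations in one block.** There are C(6,3) = 20 equally likely sequences. An allocation is certain when one arm's three places are already used.

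| Certain allocations in the block | Sequences |
|---|---|
| 1 | 12 |
| 2 | 6 |
| 3 | 2 |

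Mean = (12×1 + 6×2 + 2×3) / 20 = 30 / 20 = 1.5 of 6 = 25%. The closed form agrees: with m = 3 places per arm, 2m/(m+1) = 6/4 = 1.5.

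**Whole trial.** Expected number = 5 × 1.5 = 7.5 of 30. The minimum is 5 × 1 = 5 (16.7%) and the maximum 5 × 3 = 15 (50%). Convolving the five blocks gives P(6 to 9) = 0.1944 + 0.2592 + 0.2268 + 0.1431 = 0.82.

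**Best guess.** Suppose the observer always guesses the arm with more places left, and tosses a coin when they are equal. The chance of being right at positions 1 to 6 is 0.5, 0.6, 0.6, 0.7, 0.7 and 1.0. The sum is 4.1, and 4.1 / 6 = 68.3%, against 50% with no information.

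**Effect of varying the block size.** This was simulated with 4,000 runs of 30 patients. The observer knows which sizes are possible but not which is in use.

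| Block sizes | Certain | Best guess right |
|---|---|---|
| 6 only | 25.0% | 68.3% |
| 4, 6 | 5.7% | 68.8% |
| 2, 4, 6 | 3.9% | 69.7% |
| 4, 6, 8 | 2.2% | 67.5% |

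Varying the size removes most of the certainty but hardly changes the best-guess rate.

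The simulation drew sizes freely and cut the list at 30. If the sizes are made to sum to 30 and the observer knows this, patient 30 is always certain. The share is then at least 1/30 = 3.3%, not 2.2%. The constraint should therefore be undisclosed too.

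**The case against.** The strongest objection is that the harm needs a step the article does not describe. Nothing says that the therapist screens, judges eligibility or schedules enrolment, and an article may leave that detail to the full protocol. Section 2.5 also describes a standardised interview and audiological testing at another hospital. Allocation is made after baseline by someone other than the therapist. If the segregation rule lasts through the trial, it would block the route from the therapist's inference to those who recruit. A fixed block of 6 is also an ordinary choice, and varying it leaves the best-guess rate almost unchanged.

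Much of this stands. It limits the conclusion to a risk, and it shows that varying the block size is not enough alone. It does not remove the point. The safeguards protect the list, whereas the inference does not need the list. The segregation rule can be read as lasting for the whole trial or as starting afresh with each patient; on the second reading it comes after that patient's enrolment decision. Section 2.4 excludes the code holder from treatment and analysis, and the coordinator from data collection, but excludes neither the coordinator nor the therapist from enrolment.

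A reader might infer more than the text supports:

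- **That a quarter of allocations were in fact known.** The 25% is an expectation, for an observer with complete knowledge, under assumptions about ratio and stratification.
- **That publication disclosed the block size to the clinic during recruitment.** The text gives March 2012 to June 2013 for the trial. It does not show that the article appeared before recruitment ended or that clinic staff knew the size.
- **That treatment takes place in the recruiting clinic.** Section 2.1 says only where patients are recruited.
- **That any bias would be beyond repair.** THI has a baseline, and the Figure 3 caption includes a before-phase HRV measurement, so measured imbalance can be examined and adjusted for.

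**Conclusion.** The point holds as an avoidable predictability risk in a design rule that the article states, not as evidence that concealment failed. Someone with the block size and the ordered allocations could deduce 7.5 of 30 on average, and at least the last patient of every block. This rests on 1:1 unstratified blocks and on treatment starting in randomisation order. Whether it could bias the comparison depends on whether such a person can influence enrolment, which the article leaves open. The change is worth making because it costs almost nothing.

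**What to change.** For patients not yet randomised:

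1. Replace the fixed block size with randomly varying, undisclosed sizes, for example 4, 6 and 8, arranged to sum to the number still to be randomised (30 if none has been). Keep the sizes and the total constraint out of documents that clinic staff see.
2. Have eligibility signed off before allocation is released, by someone unaware of earlier allocations. This deals with the best-guess rate, which varying the sizes does not.

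The separately held codes and allocation after baseline already exist and should stay.

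The cost is a regenerated list and a named person for the sign-off. If recruitment stops inside a block of 8, the arms could differ by up to 4 (4:0 at mid-block), against up to 3 inside a block of 6. If recruitment reaches the planned total, the arms are balanced.

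If recruitment is already complete, report who judged eligibility and whether that person knew earlier allocations. Compare baseline characteristics of patients at forced positions with the others, and adjust for measured baseline imbalance. That cannot correct unmeasured selection.

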### 2.5. Interventions

This trial is a randomized controlled study. Participants will receive acupuncture for 3 weeks (Figure 1) (twice per week). All candidates go through a standardized interview and receive more information about the study and the treatments. They also undergo audiological testing of hearing thresholds, minimal masking levels, and loudness discomfort levels carried out by an audiologist in Tongren Hospital affiliated to Capital Medical University ([name]).

Timepoints are as follow: visit 1: screening, visit 2: treatment initiation, participants will receive acupuncture for 3 weeks, visit 3: 3 weeks later of first acupuncture, followup and treatment finish.

Patients who meet the inclusion criteria and none of the exclusion criteria are randomized to one of two treatment groups. Group A will receive verum acupuncture (creating deqi sensation). Group B will receive shallow acupuncture (not creating deqi sensation).

Acupuncture points are selected as follow (Figure 2).

Patients are stimulated by 5 main acupoints: Baihui (Du-20), Shenting (Du-24), Tinghui (GB-2), Waiguan (SJ-5), and Zulinqi (GB-41). The acupoints are stimulated continuously by the true needles or the shallows for 20 minutes per session. 

Acupuncture is performed with sterile needles by one therapist ([name]) with more than 22 years of experience and an acupuncture license from the Chinese medicine practitioner from the Ministry of Health of China. Treatment will be conducted over a period of 3 weeks, at a frequency of 2 sessions/week. No additional treatment is allowed.

### 2.6. Primary Outcome Measures

HRV indexes are measured using a digital 12 leads ECG-Holter machine (Mortara Instruments, USA). Within frequency domain, power in low frequencies (LF; 0.04–0.15 Hz), and in high frequencies (HF; 0.15–0.4 Hz) are calculated for each 5-minute density spectrum by integrating the power spectral density in the respective frequency bands. The HF/LF ratio also is analyzed [25]. HRV is measured at the first acupuncture, as well as the last acupuncture (Figure 3).

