### 2.8. Data Analysis

We use paired *t*-tests and two-way ANOVA with one repeated measure to analysis the data of 30 tinnitus patients. Post hoc analyze is performed using Tukey test. The level of significance is defined as *P* < 0.05. 

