**Figure 3 fig3:**
[figure not shown]
Sequence for heart rate variability (HRV) testing. The data before measurement phases (a), during (b–e), and after (f) were measured and statistically analyzed.

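### The primary outcome is three HRV indexes at two sessions with no primary index, session or contrast named, so the false-positive risk for the primary claim is up to about 14% (three tests) or 26% (six tests), not 5%

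*Protocol article*

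**What the plan says.** The protocol article names a domain, not a variable, as primary. Its Abstract says: "The primary outcome measure is heart rate variability, which is measured at the first acupuncture, as well as the last acupuncture".

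Section 2.6, on primary outcome measures, gives the content. Two indexes come from the spectrum: "power in low frequencies (LF; 0.04–0.15 Hz), and in high frequencies (HF; 0.15–0.4 Hz) are calculated for each 5-minute density spectrum". A third is built from them, and the timing follows: "The HF/LF ratio also is analyzed [25]. HRV is measured at the first acupuncture, as well as the last acupuncture". The three indexes are not ranked, and neither session is preferred.

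The Figure 3 caption adds the phases within a session: "The data before measurement phases (a), during (b–e), and after (f) were measured and statistically analyzed". That is one phase before, four during and one after, so six.

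Section 2.8 gives the analysis: "We use paired *t*-tests and two-way ANOVA with one repeated measure to analysis the data of 30 tinnitus patients". Tukey's test is the post hoc procedure. On error control the section says: "The level of significance is defined as *P* < 0.05". It does not say which factor is the repeated one, what the paired t-tests compare, or which result decides the trial.

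**The concern.** A primary outcome should identify the one result, or the short list of results under a joint error rate, on which the trial's claim rests. Here the aim is the effect of deqi on HRV, and that claim could rest on LF, HF or the ratio, at either session. Each could be read against the same 5% threshold.

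Tukey's test controls pairwise comparisons within one ANOVA. It does nothing across three indexes, across ANOVAs fitted separately, or for the paired t-tests. The paired t-tests matter because the Discussion asks whether either type of acupuncture acts through HRV, and a within-arm before-after test could seem to answer that without any comparison of arms.

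Nothing else in the article shows which test was meant. The Discussion says that the sample size could not be calculated, so there is no power assumption tied to one index or session. The choice could therefore be made with the results in view.

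**Working it through.** **Inputs**

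- Indexes: 3 (LF, HF, HF/LF), Section 2.6.
- Sessions: 2 (first and last), Abstract and Section 2.6.
- Phases per session: 6 (a; b, c, d, e; f), Figure 3 caption.
- Threshold: 0.05, Section 2.8.
- Patients: 30, Sections 2.1 and 2.8. Taking 15 per arm is an assumption, since equal allocation is not stated.

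**Step 1: the plan's own figure.** The only error rate given is 5%. For one test, 1 − 0.95^1 = 5.0%. No familywise rate, effect size, SD or power is stated, so nothing else can be reproduced.

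**Step 2: how many analyses the stated method implies.** Each patient has two repeated factors, session (2) and phase (6). The ANOVA in Section 2.8 has one repeated measure. Assume that its other factor is group.

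- Phase as the repeated factor: one ANOVA per index and session, 3 × 2 = 6.
- Session as the repeated factor: one ANOVA per index and phase, 3 × 6 = 18, unless phases are averaged.
- Phases averaged, or all time points taken as one sequence: one ANOVA per index, 3.

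The article does not choose between these. None of them gives a single test.

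**Step 3: chance of at least one false positive in k tests at 0.05, if independent.** The formula is 1 − 0.95^k.

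- k = 3: 1 − 0.95^3 = 14.3%
- k = 6: 1 − 0.95^6 = 26.5%

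Whatever the correlation, the rate cannot exceed k × 0.05, which is 15% and 30%.

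**Step 4: allowing for correlation.** The ratio is a function of LF and HF, and the sessions share patients, so the tests are not independent. Trials were simulated with no true effect and 15 per arm. The variance shares and LF–HF correlations are assumptions, because the article gives none.

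- Group-by-phase interaction, 3 indexes, one session: 12–14%.
- Group-by-phase interaction, 3 indexes, two sessions (6 tests): 23–25%.
- Group main effect, 3 indexes, two sessions (6 tests): 20–21%.

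These used 6,000 trials per setting, a patient variance share of 0.4–0.7, a session share of 0.2 and an LF–HF correlation of 0–0.7. A second simulation used 2,500 trials per setting, shares of 50% patient, 20% session and 30% phase, and a correlation of 0.3–0.8. For six between-arm t-tests on the mean of phases b–e minus phase a, it gave 22–24%.

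**Step 5: wider readings, which the article does not state.**

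- All 18 ANOVA effects (group, phase and interaction, for 3 indexes and 2 sessions): 52–54% simulated.
- 36 between-arm t-tests, one per index, session and phase: 37–62% simulated.
- 60 uncorrected within-arm paired t-tests (phase a against each of b–f: 5 × 2 arms × 2 sessions × 3 indexes): 86–88% simulated.

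**Step 6: after the change.** One named contrast returns the rate to 5%. Holm over a declared list also holds it at 5%; its strictest step is 0.05/3 = 0.0167 or 0.05/6 = 0.0083. For the price in power, take a two-sided normal approximation, power ≈ Φ(d√(n/2) − z), with n = 15 per arm and d an assumed standardised difference. At d = 0.8, d√(n/2) = 0.8 × √7.5 = 2.19. Power is Φ(2.19 − 1.96) = 59% at 0.05 and Φ(2.19 − 2.39) = 42% at 0.0167. At d = 1.0 the figures are 78% and about 64%. Holm does no worse than this strictest step.

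**The case against.** The strongest objection is that the number of tests is unknown and may be small. A repeated-measures ANOVA takes the levels of its repeated factor together, and Tukey then covers the pairwise comparisons within it. If the repeated factor is session, with phases summarised, or all time points in sequence, both sessions sit in one ANOVA per index and only three analyses remain. The wording on the ratio could also mark it as supplementary, which would leave two indexes and 1 − 0.95^2 = 9.75%. This stands as a limit on the size: 26% is the figure for six tests, not a fixed property of the plan.

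It is also fair that a condensed article may leave multiplicity rules, the factors of the ANOVA and the targets of the t-tests to a fuller document. The absence of an alpha adjustment is therefore not the point. The point is what Section 2.6 does fix: several indexes and two sessions as primary, unranked. Which variable is primary belongs where the primary outcome is defined.

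A reader might go further and infer that all 3 × 2 × 6 = 36 values are each tested at 5%, so that a false-positive primary result is more likely than not. The article does not support this. The 36 are values per patient, not tests. Section 2.8 names no uncorrected between-arm comparison phase by phase. Rates above one half arise only if single cells, every ANOVA effect or every paired t-test is taken as primary evidence.

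Finally, this is a small mechanism study that openly acknowledges its limited sample. That tempers how serious the defect is, but it does not remove it.

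**Conclusion.** The point holds in this form: the primary outcome is plural, with no primary index, session or between-arm contrast, and the stated error control does not reach across its parts. Against a nominal 5%, the chance of at least one false positive is up to about 14% with one test per index and up to about 26% with one per index and session. It would be higher if single phases or within-arm t-tests were also allowed to carry the claim.

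The figures assume that group is the second ANOVA factor, that arms are equal and that any one significant test would be reported as a primary result. The simulated figures rest further on the assumed variance shares and correlations, though they moved little across the settings tried for three and six tests. The documents do not show that a false positive is likely, nor that any one index or session was the intended primary. The defect should be corrected because it leaves the main claim open to selection, but it does not by itself invalidate a study of this kind.

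**What to change.** In Sections 2.6 and 2.8, before data are seen, name one HRV index and one verum-minus-shallow contrast as primary, and state which session it uses. One example is HF power averaged over phases b–e, adjusted for the pre-needling phase a. The choice of index and session is the sponsor's: the article's parasympathetic argument points to HF, while its remark on sympathovagal balance would equally suit the ratio. Make the remaining indexes, session and phases, and the within-arm paired t-tests, secondary.

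Alternatively, keep a short declared list of between-arm contrasts (three indexes, or three indexes at two sessions) and apply Holm's procedure across it. In either case, state which factor the ANOVA treats as repeated.

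The cost is about one paragraph, with no change to treatment or measurement. With a single primary contrast, the demoted indexes can no longer carry the main claim. With Holm, each test has less power, by at most the amounts in step 6 for a list of three and by more for a list of six.
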